### Protocol for analysis of bite force

Bite force will be measured using a digital dynamometer (DMD model, Kratos Equipamentos Industriais Ltda, Cotia, SP, Brazil) adapted for oral conditions. This device is an electronic bite force meter composed of a bite fork and module with a digital display connected by a wire. The readings will be made in the region of the first molars in Angle Class I [33] and free of caries. The volunteer will receive prior orientation and training to become familiar with the device. Six readings will be made – three on the right side and three on the left side, alternating sides between readings. Each reading will last five seconds and will be separated by a one-minute rest period. Bite force will be evaluated prior to the onset of treatment, at the end of treatment and 30 days after the end of treatment. The results will be computed and analysed statistically.

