**Methods:**

The children will be randomly allocated to four groups of 19 individuals: G1 - low-level laser; G2 - occlusal splint; G3 - placebo laser; and G4 - control (without bruxism). The BTS TMJOINT electromyography will be used to determine muscle activity and a digital gnathodynamometer will be used to measure bite force. Salivary cortisol will be analysed at baseline as well as one and six months after treatment. Two-way ANOVA will be employed and complemented by Tukey’s test.

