The frequency of bruxism is high in childhood, with prevalence rates ranging from 13.5 to 33% [14, 15] and this condition can cause harm to the stomatognathic system. Childhood bruxism is difficult to diagnosis and ideal treatment has not yet been established. Physical therapy is currently used to treat this condition and the most commonly employed methods are transcutaneous neuromuscular stimulation, microcurrent electrical neuromuscular stimulation, cryotherapy, ultrasound, infrared therapy, kinesiotherapy, massage therapy, acupuncture, low-level laser therapy (LLLT) and occusal splint usage [16, 17]. According to Solberg et al. [18], an occlusal splint reduces muscle activity and provides greater patient comfort. Occlusal splint usage seems to reduce tooth grinding, masticatory muscle activity and orofacial pain [19]. Although occlusal splints are widely employed for the treatment of bruxism, no specific strategy has been established for the cure of this condition. Thus, further studies are needed [18, 20].

LLLT is a non-invasive, low-cost treatment. The irradiation of trigger points constitutes effective treatment for orofacial pain as well as the reduction of swelling and hyperemia [21]. Acupuncture has also been successfully used for the treatment of bruxism, achieving a reduction in the activity of the masseter and anterior temporal muscles as well as a reduction of anxiety [22]. The stimulation of particular acupoints can alter blood circulation dynamics and promote muscle relaxation, thereby alleviating muscle spasms, inflammation and pain. Moreover, such stimulation leads to the release of hormones, such as cortisol and endorphins, thereby promoting an analgesic effect [23]. The stimulation of acupoints can be achieved with the use of needles, infrared irradiation, electrical current or laser [24]. The latter method is indicated for children because it is painless and has a shorter exposure time per acupoint [25–27]. However, the use of LLLT over acupoints has not yet been tested on children with bruxism. Therefore, the aim of the proposed study is to investigate changes in maximum bite force (measured using a gnatodynamometer) one and six months after low-level laser therapy over acupoints and occlusal splint usage compared to muscle hyperactivity at baseline in children. The secondary outcomes are the measure of pain (VAS scale), muscle activity (using the BTS TMJOINT® electromyograph) and salivary cortisol.

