For G2, the maxillary occlusal splint will be made with transparent acrylic resin and used on with upper arch with palatal and occlusal coverage. Impressions of the maxillary and mandibular arches will be made in alginate, poured in dental stone and mounted on a semi-adjustable articulator. The splint will be made in two layers of rose-colored wax and adapted to the maxillary teeth. The splint will have a thickness of 3 mm, contact with all teeth in centric relationship, distocclusion of the posterior teeth in laterality and protrusion, avoiding interferences on the swinging side with the canine guide extending from the vestibular to the lingual direction enough to prevent perforation and increase resistance to impact. An expander will also be installed so the splint will be able to accompany the growth dynamics. Following the protocol described by Hachmann et al., [20] the children will use the occlusal splint only at night for two months, with weekly adjustments of one quarter turn.

In G4 (control), children without bruxism will be evaluated. Therefore, this group will not be submitted to any bruxism treatment. This will be the control group.

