### Study variables

All groups will be submitted to the evaluation of muscle activity using the BTS TMJOINT® electromyograph and the evaluation of bite force with a gnatodynamometer at baseline as well as one and six months after treatment. Salivary cortisol will be measured at baseline and after the therapeutic intervention.

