### Protocol for evaluation of salivary cortisol

Saliva will be collected using a swab, which consists of a small ball of cotton on the end of a thin plastic tube. The swab will remain in the mouth for two minutes. The cotton will subsequently be placed in a centrifugation tube and stored at −20 °C until analysis [36]. Stress will be determined by the quantification of salivary cortical prior to the onset of treatment and on Day 50. For the study of circadian rhythm of cortisol, two saliva samples will be collected at the home of the participant after at least one hour of fasting and after oral hygiene with water: one at 9 am and one before sleep. The collections will be performed on a Sunday with orientation and using the recommendations of the manufacturer. The samples will be delivered the following day for analysis at Nove de Julho University.

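### Bite force, the primary outcome, has two incompatible visit schedules, and the Day 50 cortisol sample falls after the laser course but probably during splint use

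*Protocol article*

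**What the plan says.** **Bite force.** The Background gives the aim as studying "changes in maximum bite force (measured using a gnatodynamometer) one and six months after low-level laser therapy over acupoints and occlusal splint usage". It lists pain, muscle activity and cortisol as secondary outcomes, so bite force is the primary outcome. Study variables agrees with the aim and adds baseline: "the evaluation of bite force with a gnatodynamometer at baseline as well as one and six months after treatment". The section on bite-force analysis, which staff would follow when measuring, says: "Bite force will be evaluated prior to the onset of treatment, at the end of treatment and 30 days after the end of treatment".

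**Cortisol.** The Abstract (Methods) says: "Salivary cortisol will be analysed at baseline as well as one and six months after treatment". Study variables says: "Salivary cortisol will be measured at baseline and after the therapeutic intervention". The cortisol section places the samples "prior to the onset of treatment and on Day 50".

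**Treatment periods** (Randomisation and interventions).
- G1 has twelve laser sessions, two a week, and G3 has the same course as placebo.
- In G2, "the children will use the occlusal splint only at night for two months". The switched-off laser is also positioned over the same points in G2.
- G4, the children without bruxism, has no treatment.
- G3 moves to complementary bruxism treatment once 30 days of follow-up have passed. The start of those 30 days is not stated.

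**The concern.** The protocol does not fix when the primary outcome is measured. A team following the bite-force section would collect an end-of-treatment reading that the aim does not mention and would never collect the six-month reading that the aim requires. Each schedule has support in the text, so the reported time point could be chosen after the data are seen. The choice matters because G3 changes treatment between the one-month and six-month readings, if not earlier, so the two readings answer different questions.

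For cortisol, one calendar day is applied to arms whose treatments last different lengths of time. The Discussion names the comparison of laser with splint as the main objective. On Day 50 that comparison may set children who have finished treatment against children who have not.

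**Working it through.** **Step 1. Bite-force schedules side by side.**

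| Reading | Background (aim) | Study variables | Bite-force section |
|---|---|---|---|
| Baseline | implied | yes | yes |
| End of treatment | no | no | yes |
| One month / 30 days after | yes | yes | yes |
| Six months after | yes | yes | no |

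Only baseline and about one month appear throughout. This needs no arithmetic and no assumption.

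**Step 2. Cortisol schedules.** The Abstract has two post-treatment samples, at one and six months. The cortisol section has one, on Day 50. Study variables has one, undated. The firm conflict is between the Abstract and the cortisol section, in both the number and the dates of samples.

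**Step 3. When treatment ends.** The article does not define Day 1. Assume it is the first laser session or the first splint night.
- Laser and placebo laser: 12 sessions ÷ 2 per week = 6 weeks. With gaps of 2/5, 3/4 or 4/3 days, the last session is on Day 38, 39 or 40. Six full weeks end on Day 42. Range: Day 38–42.
- Splint: two months, taken as 8 weeks to 61 days. Range: Day 56–61.

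**Step 4. Where Day 50 falls.**
- G1 and G3: 50 − 42 = 8 and 50 − 38 = 12, so 8–12 days after the course ends.
- G2: 56 − 50 = 6 and 61 − 50 = 11, so 6–11 days before splint use ends.

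Day 50 is therefore post-intervention in G1 and G3 but not in G2.

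**Step 5. Bite-force visits, taking treatment end in G2 as the end of splint use.**

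| Visit | G1, G3 | G2 |
|---|---|---|
| End of treatment | Day 38–42 | Day 56–61 |
| 30 days later | Day 68–72 | Day 86–91 |
| Six months (182 days) later | Day 220–224 | Day 238–243 |

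Each treated arm is measured at the same interval from its own treatment end. Time since baseline differs by 56 − 42 = 14 to 61 − 38 = 23 days, about two to three weeks.

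If treatment end in G2 instead meant the last switched-off laser session, and those sessions followed the G1 schedule (not stated for G2), the end-of-treatment visit would fall on Day 38–42, with splint use still under way. This is why the term needs a definition.

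**Step 6. G3.** If its 30 days of follow-up run from treatment end, the complementary treatment starts at about the 30-day visit, and a six-month reading has no intact placebo comparator. If they run from enrolment, the change would come before the twelve sessions are finished (Day 30 against Day 38–42). The article does not say which is meant.

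**The case against.** The strongest defence is that much of the schedule can be read coherently.

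- **A reader might infer that bite force, too, is compared at different treatment phases by arm.** The text does not support this. Every bite-force version is anchored to treatment, so with splint end as the anchor in G2 the treated arms are at the same phase. Only time since baseline differs. Anchoring to treatment end is an ordinary choice when durations differ, and nothing in the article shows that two to three weeks would bias bite force at ages six to eight.
- **A reader might infer three mutually exclusive cortisol schedules.** The undated wording in Study variables is compatible with Day 50 in G1 and G3. It fails only in G2.
- **The bite-force lists could be additive**, giving baseline, end of treatment, one month and six months. No section states that combined schedule, and the bite-force section reads as a complete list.
- **The day counts rest on an undefined Day 1.** This stands as a limit. Splint use would be over by Day 50 only if it had begun at least 6–11 days before Day 1.
- **G4 has no treatment end**, but it is a reference group without bruxism. Its missing anchor does not disturb G1 against G2 or G3. One baseline-counted window could not match both Day 68–72 and Day 86–91, so matching should not be asked for.

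None of this removes the contradiction over bite force or the Day 50 problem in G2.

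**Conclusion.** The point holds. The assessment times of the primary outcome are not uniquely determined: of the three post-baseline times mentioned, only the one-month or 30-day reading appears in every section. This rests on the text alone.

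The secondary part is cortisol. The Abstract and the cortisol section disagree outright. Under the stated assumption about Day 1, Day 50 is 8–12 days off treatment in G1 and G3, and 6–11 days short of the end of splint use in G2. That finding is probable rather than certain, because the time origin is undefined. The effect on the cortisol comparison cannot be sized from the article. The point does not extend to a phase mismatch in the bite-force visits.

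**What to change.** 1. Reconcile the Abstract, Background, Study variables, bite-force and cortisol sections into one visit schedule with a defined Day 1. State whether treatment end in G2 means the switched-off laser sessions or the splint.
2. Name the 30-day post-treatment visit as the primary bite-force time, since it is the only post-baseline visit on which the sections agree. Take that reading before G3 receives its complementary treatment, and state from when the 30 days of follow-up in G3 are counted.
3. If the six-month reading is kept, add it to the bite-force section and label it as having no intact placebo comparator. Otherwise delete it from the Background and Study variables.
4. Replace Day 50 with a cortisol sample at a post-treatment visit defined the same way in each treated arm.
5. Give G4 one stated schedule counted from baseline, and record days since baseline for every child.

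**Cost.** Mostly wording, but not only that. With splint end as the anchor in G2, a cortisol sample at the 30-day visit moves later by 68 − 50 = 18 to 72 − 50 = 22 days in G1 and G3, and by 86 − 50 = 36 to 91 − 50 = 41 days in G2. It then estimates a post-treatment effect rather than a Day 50 effect, which should be stated openly. These changes concern measurement times only. No treatment rule or duration is proposed.

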### Protocol for evaluation of occlusal contacts

Occlusal contacts will be determined during the electromyographic analysis following the method described by Ferrario et al. [34]. To evaluate symmetry of the temporal and masseter muscles, the overlap percentage coefficient will be computed, which is an index of the distribution of the symmetry of muscle activity ranging from 0% (asymmetry) to 100% (perfect symmetry). The torque coefficient will also be determined, which is the lateral displacement in contralateral activity of the masseter and temporal muscles ranging from 0% (absence of lateral displacement force) to 100% (maximum lateral displacement force) [27, 31]. The total mean activity of the masseter and temporal muscles will be analysed as area over time [27, 32–35]. A clinical examination will then be performed to determine the type of occlusion based on the Angle classification [33], which is the most practical, traditional system and is considered the gold standard in the literature. This system is based on anteroposterior relationships of the maxilla and mandible:Angle Class I (neutroclusion) – The mesiovestibular cusp of the permanent maxillary molar makes contact with the buccal groove of the permanent mandibular first molar;Angle Class II (distoclusion) – The mesial groove of the permanent mandibular first molar makes contact with the mesiobuccal cusp of the permanent maxillary first molar.Angel Class III (mesioclusion) – The mesial groove of the permanent mandibular first molar makes contact anterior to the mesiobuccal cusp of the permanent maxillary first molar.

### Protocol for evaluation of salivary cortisol

Saliva will be collected using a swab, which consists of a small ball of cotton on the end of a thin plastic tube. The swab will remain in the mouth for two minutes. The cotton will subsequently be placed in a centrifugation tube and stored at −20 °C until analysis [36]. Stress will be determined by the quantification of salivary cortical prior to the onset of treatment and on Day 50. For the study of circadian rhythm of cortisol, two saliva samples will be collected at the home of the participant after at least one hour of fasting and after oral hygiene with water: one at 9 am and one before sleep. The collections will be performed on a Sunday with orientation and using the recommendations of the manufacturer. The samples will be delivered the following day for analysis at Nove de Julho University.

### Protocol for evaluation of pain

The Wong-Baker FACES Pain Rating Scale will be used to evaluate pain. This is a self-reported scale that consists of a number of faces ranging from happy to crying. The scale will be explained to the children and they will indicate the face that best corresponds to their level of pain before and after treatment (Additional file 5).

### Statistical analyses

Descriptive statistics will be used first for the determination of point estimates. The Shapiro-Wilk test will be used to determine the normality of the data. The chi-square test, Student’s t-test and ANOVA will be employed for the analysis of associations between variables, with the level of significance set at 5% (*p* < 0.05). After the analysis of data distribution, ANOVA will be used for the evaluation of residuals and parametric tests will be used for the determination of pre-treatment conditions. Interval estimates will be used for the variables of interest to determine the estimates and perform comparisons. When necessary, transformation methods or non-parametric tests will be used in the data analysis.

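### The tests named for bite force and EMG, measured three times per child, fix neither a within-child error term nor a baseline covariate, and Abstract and Methods disagree on pairwise error control

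*Protocol article*

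**What the plan says.** The Background makes bite force the main outcome and frames it as change: "the aim of the proposed study is to investigate changes in maximum bite force". Study variables schedules EMG and "bite force with a gnatodynamometer at baseline as well as one and six months after treatment". The bite force section also gives three occasions, but different ones: "Bite force will be evaluated prior to the onset of treatment, at the end of treatment and 30 days after the end of treatment". Either way, each child contributes three correlated values.

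On analysis, the Abstract says "Two-way ANOVA will be employed and complemented by" Tukey's test. The Statistical analyses section does not mention a two-way layout or Tukey. It lists the chi-square test, Student's "t-test and ANOVA will be employed for the analysis of associations between variables, with the level of significance set at 5" percent. Baseline appears there only in the statement that "parametric tests will be used for the determination of pre-treatment conditions". The fallback is "When necessary, transformation methods or non-parametric tests will be used in the data analysis", which deals with distributional shape and not with correlation between visits.

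No section names a repeated-measures or mixed model, a paired test, a child-level term or a baseline covariate.

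**The concern.** When three values come from one child, variation splits into a between-child and a within-child part. The group main effect should be judged against the first and the group-by-time interaction, which carries the treatment effect, against the second. An ANOVA that pools the two is wrong in opposite directions for the two tests. The protocol names its tests without saying which form applies, so an analyst could follow the text and choose the wrong one.

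The disagreement between Abstract and Methods adds to this. One place controls error over pairs of groups, and the other lists tests at 5% with no adjustment mentioned. Several analyses therefore fit the text and could lead to different conclusions. Baseline bite force is collected anyway and would sharpen the comparison, but the only role stated for it is a pre-treatment test.

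**Working it through.** **Inputs.** From the protocol: three occasions per child (T = 3); four groups, three of them with bruxism; nominal level 5%; 15.75 children per group before the dropout allowance, taken here as 16. Assumed, because the protocol gives no value: equal variances, the same correlation ρ between any two visits, ρ of 0.3, 0.5 or 0.7, and for power a 0.8 SD shift in one group at both follow-ups.

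**Step 1: why independent errors go wrong.** With total variance σ² and no true effects, the expected mean squares are:
- group: σ²[1 + (T − 1)ρ] = σ²(1 + 2ρ)
- group by time: σ²(1 − ρ)
- pooled error of an ordinary two-way ANOVA: σ²

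The group F ratio is thus inflated by 1.6, 2.0 and 2.4 at ρ = 0.3, 0.5 and 0.7, and the interaction F ratio is shrunk to 0.7, 0.5 and 0.3 of its proper size.

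**Step 2: type I error.** In large samples the group test rejects with probability P(χ² > c/(1 + 2ρ)), where c is the 5% critical value on (groups − 1) degrees of freedom. With three groups this is 0.05^(1/(1 + 2ρ)):
- ρ = 0.3: 0.05^0.625 = 0.154
- ρ = 0.5: 0.05^0.5 = 0.224
- ρ = 0.7: 0.05^0.417 = 0.287

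Simulation at 16 per group agrees:

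| Independent-error ANOVA, nominal 5% | ρ = 0.3 | ρ = 0.5 | ρ = 0.7 |
|---|---|---|---|
| Group effect, 3 groups | about 15% | 22% | 28–29% |
| Group effect, 4 groups | 18% | 27% | 35% |
| Any false Tukey difference on marginal group means, 4 groups | 18% | 26% | 34% |
| Group by time, 3 groups | 0.9% | 0.1–0.2% | about 0% |

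Tukey's test does not repair the problem, because it uses the same pooled error. With the child kept as a random effect, both tests return to about 5%.

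**Step 3: power of group by time** (three groups, 16 per group, 0.8 SD in one group at both follow-ups):

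| | ρ = 0.3 | ρ = 0.5 | ρ = 0.7 |
|---|---|---|---|
| Independent errors | about 25% | 18% | 9% |
| Within-child error | 48% | 64% | 88% |
| Share of power lost | 1 − 25/48 = 48% | 1 − 18/64 = 72% | 1 − 9/88 = 90% |

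**Step 4: what baseline adjustment adds when the error term is already right.** At one follow-up visit, ANCOVA has variance (1 − ρ²) relative to the unadjusted comparison: 0.91, 0.75 and 0.51. Relative to change scores, whose variance is 2(1 − ρ), the ratio is (1 − ρ²)/[2(1 − ρ)] = (1 + ρ)/2: 0.65, 0.75 and 0.85. For a two-group comparison with a 1 SD difference and 16 per group, power is 81% unadjusted and 84%, 90% and 98% with ANCOVA.

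**The case against.** The strongest reply is that the protocol never says the ANOVA ignores the child. Its factors and error term are unstated. A group-by-time repeated-measures ANOVA is often called simply a two-way ANOVA, and a Student's t-test may be paired. The stated aim concerns changes, and an ANOVA with Tukey on change scores or at one visit has one value per child. A condensed article may also leave the error term to a fuller document that is not shown. All of this stands: a reader might infer that the plan prescribes an invalid test, but the text does not establish that.

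A reader might also infer that most of the power is lost. That holds only for the group-by-time test run with independent errors at correlations of about 0.5 or more. At 0.3 the loss is about half, and a single-visit t-test loses only about 4, 10 and 17 percentage points against ANCOVA for a 1 SD difference (from Step 4). The independent-error group test rejects too often, so it is not a loss of power at all. Nor does the text commit to six unadjusted t-tests among the four groups: it lists t-tests for associations between variables, so a family error rate built on six such tests has no firm basis.

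What the reply does not remove is that the protocol does name its tests, that its two statements differ, and that neither says how three values per child or the collected baseline will be handled.

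**Conclusion.** The point holds as a badly fixed method. It does not hold as proof of a wrong one. Under independent errors, the group main effect has a type I error of about 15% to 29% with three groups and 18% to 35% with four, and the group-by-time test falls to 1% or less with the power losses shown. Under a repeated-measures or change-score form the error rates are sound, and the remaining gain is the precision from baseline adjustment. The direction of each error follows from the expected mean squares for any positive correlation. The sizes rest on the assumed correlations of 0.3 to 0.7, equal correlation between visits, 16 complete children per group and, for power, the 0.8 SD effect. None of the correlations or effect sizes comes from the protocol. The disagreement between Abstract and Methods on the named tests and on pairwise error control rests on no assumption.

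**What to change.** First reconcile the follow-up times: Study variables gives one and six months after treatment, while the bite force section gives end of treatment and 30 days later. Then state one method, identically, in the Abstract and in Statistical analyses:

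- **Model:** a linear mixed model for post-treatment bite force in G1 to G3, with group, visit, group by visit and baseline bite force as fixed effects and the correlation between a child's visits modelled. ANCOVA at one visit is an acceptable simpler form.
- **Primary result:** the adjusted between-group difference with its 95% confidence interval at one pre-named follow-up.
- **Multiplicity:** Tukey over the three pairs, or one pre-named contrast.
- **EMG:** the same model.
- **G4:** describe it alongside but keep it out of the model. It consists of children without bruxism, so its baseline differs by design and the contrast is not a randomised one.
- **Remove** the significance tests of pre-treatment conditions.
- **Later G3 data:** do not interpret them as pure placebo. The interventions section gives this group complementary treatment after 30 days of follow-up, which bears on which visit can serve as the primary one.

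The cost is wording only: no new data, no extra visits, and standard software.
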